### Data analysis

#### Quantitative data analysis

We will analyse quantitative data with the statistical computing software R. The analytical approach will be guided by the RE-AIM framework (Tables 1–5).

##### Data preparation and descriptive analyses

Patient, provider, and center level characteristics will be summarized using descriptive statistics (means ± SD or medians [IQR] for continuous variables; counts and percentages for categorical variables) overall, stratified by center, and by center type. All validated instruments will be scored according to their standard scoring protocols.

##### Missing data, attrition, and loss to follow-up

We will quantify attrition rates and assess whether loss to follow up differ by key demographic and clinical characteristics. To reduce selection bias due to differential follow-up, we will apply inverse probability of censoring weighting (IPCW) in longitudinal analyses.

##### Patients

Longitudinal patient outcome data and demographics questionnaires will be analysed and compared to data from the MAP studies. MAP cohort differs at baseline from patients receiving MHCs care. Consequently, we will use inverse probability weighting (IPW) to improve comparability. The IPW model will include key covariates (e.g., age, sex, baseline symptom severity, and prior mental health service use), creating a pseudo-population in which these covariates are balanced between groups. Weighted analyses will be used for all primary MAP vs. MHC outcome comparisons. Additionally, sensitivity analyses will be carried, restricting the sample of MAP subjects to those seeking care and/or with a comparable baseline outcome levels.

We will conduct these analyses on 2 primary cohorts:

1 Retained in care cohort (per protocol style):

This cohort includes patients who remained engaged in MHC care and completed baseline, follow up 1 and 2.

2 Care initiators cohort (intention to treat style):

This cohort will include all enrolled participants regardless of adherence or continued engagement.

For both cohorts, we will estimate intervention effects using DiD approach, comparing pre–post changes in outcomes between MHCs and the MAP cohort, depending on outcome availability and harmonization. Regression models will include center fixed effects and time fixed effects, with the DiD estimand given by the treatment-by-post (or treatment-by-time) interaction. Where multiple follow-ups are available, we will implement an event-study specification (baseline, follow-up 1, follow-up 2). We will obtain 95% confidence intervals, and *p*-values via center-level wild cluster bootstrap (1,000 draws). As a robustness check for small-sample inference, we will also report results using a Kenward–Roger/Satterthwaite-style degrees-of-freedom adjustment. For retained in care cohort, we will adjust the analyses using inverse probability of censoring weighting (IPCW) to address differential loss to follow up.

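### A cohort selected on post-baseline retention has equal primary rank with the all-enrolled cohort, and the article's two statements on the scope of IPCW do not agree

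*Protocol article*

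**What the plan says.** In the Protocol article, Quantitative data analysis, Patients: "We will conduct these analyses on 2 primary cohorts". The first, called per-protocol style, is defined as "This cohort includes patients who remained engaged in MHC care and completed baseline, follow up 1 and 2". The second, called intention-to-treat style, is defined as "This cohort will include all enrolled participants regardless of adherence or continued engagement". No order or decision rule links them.

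The same estimator serves both: "For both cohorts, we will estimate intervention effects using DiD approach, comparing pre–post changes in outcomes between MHCs and the MAP cohort". MAP is described under The external control cohort as a probability sample of Ukrainian adults. The only restrictions stated for MAP are sensitivity analyses by care seeking or baseline outcome level. The inverse probability weights that make MAP comparable use covariates such as age, sex, baseline severity and prior service use.

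IPCW is mentioned twice. Under Missing data, attrition, and loss to follow-up: "To reduce selection bias due to differential follow-up, we will apply inverse probability of censoring weighting (IPCW) in longitudinal analyses". Under Patients: "For retained in care cohort, we will adjust the analyses using inverse probability of censoring weighting (IPCW) to address differential loss to follow up". The second passage is silent on the all-enrolled cohort.

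The Sample size calculation section names one primary outcome, PHQ-9 change to follow-up 4, tested at a two-sided 5% level with about 400 enrolled.

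**The concern.** Staying in care and completing two follow-ups can both depend on how the patient is doing. A cohort chosen on these events is therefore partly chosen on the outcome. In the MHC group the selection includes an engagement condition that MAP members cannot meet, so a difference in change between the groups can arise without any effect of care.

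With two primary cohorts of equal rank, one primary outcome has two primary answers. If they differ, the article does not say which one decides.

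The evaluation is meant to guide national scale-up, and that question concerns everyone who starts care. The all-enrolled cohort answers it. That is also where outcomes go missing after dropout, so it is where the handling of loss to follow-up most needs to be clear.

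**Working it through.** **1. The plan's own figure.** Inputs from the Sample size calculation section: SDs 5.97 and 5.50, correlation 0.546, N = 400, m = 50, two-sided 5%, 80% power.

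- Var(change) = 5.97² + 5.50² − 2 × 0.546 × 5.97 × 5.50 = 30.04, so SD = 5.48.
- Detectable effect = (1.960 + 0.842) × 5.48 × √(DE/400), with DE = 1 + 49 × ICC.

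| ICC | DE | Stated | Recomputed, 400 analysed | 80% retained | 70% | 60% |
|---|---|---|---|---|---|---|
| 0.01 | 1.49 | 0.94 | 0.937 | 1.01 | 1.06 | 1.13 |
| 0.02 | 1.98 | 1.08 | 1.080 | 1.15 | 1.19 | 1.25 |
| 0.05 | 3.45 | 1.43 | 1.426 | 1.47 | 1.51 | 1.55 |

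The last three columns use the same formula with N = 400 × share retained and m = 50 × share retained. The retention shares are assumptions, as the article gives none. The stated values reproduce only with all 400 enrolled analysed, so they describe the all-enrolled cohort and not the retained one.

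**2. Can the planned adjustments remove the selection?**

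- Baseline weighting balances what is known at entry. Retention is decided later.
- DiD removes fixed differences in level. Selection related to improvement acts on the change itself.
- IPCW can remove it if the weight model holds the post-baseline variables that drive retention.
- The retained cohort is defined through follow-up 2 while the primary outcome is at follow-up 4, so outcomes can also go missing inside that cohort.

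**3. Size of the selection, by simulation with no true effect.** Change scores use the SDs and correlation above. Everything else is assumed: MAP not selected; 60 or 80% of MHC patients retained; odds of retention multiplied by 1.25, 1.5 or 2.0 per SD of interim improvement; interim–final correlation of change 0.5 or 0.7. Negative values favour the MHCs.

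| Handling of the retained cohort | Spurious DiD, PHQ-9 points |
|---|---|
| Unweighted | −0.12 to −0.96 |
| IPCW on baseline PHQ-9 only | −0.08 to −0.69 |
| IPCW with the true post-baseline driver | about 0 |

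The plan weights this cohort, so the unweighted row is not what it would report. If improvers are the ones who leave, the signs reverse.

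**4. Two primary tests.** Assume success were claimed when either cohort is significant at 5%. For nested means of independent patients the correlation is √(share retained):

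| Share retained | Correlation | Error, either test |
|---|---|---|
| 60% | 0.775 | 8.0% |
| 70% | 0.837 | 7.6% |
| 80% | 0.894 | 7.1% |

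Both tests would share MAP and the eight centres, which raises the correlation. With a shared control mean as variable as the full MHC mean, the error at 60 to 80% retained is 7.3 to 6.6%. With eight centres of 50 and ICC 0.01 to 0.05 it lies between 7.6 and 6.2%.

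**5. The two IPCW statements.** The missing-data section sets no cohort limit, and the all-enrolled DiD is a longitudinal analysis, so its plain wording covers that cohort. The Patients section says that both cohorts get the DiD analysis, then names one of them for IPCW. Read together, they leave the scope for the all-enrolled cohort unsettled.

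**The case against.** The retained cohort is openly labelled per-protocol style and is reported beside the all-enrolled one. Weighting completers back to all enrolled is a standard method, and the bias vanishes if the weight model is right. The article does not list the IPCW covariates, and an article may leave these to the full plan. This stands: the cohort is not biased by definition, and the size and even the direction of any bias rest on assumptions.

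A reader might infer that dropout in the all-enrolled cohort goes unhandled. The article does not support that. The missing-data section promises IPCW without a cohort limit, and the Patients section neither says that only the retained cohort is weighted nor withdraws the general promise. What stands is an inconsistency of scope.

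A reader might also infer that MAP is wholly unselected. The article does not say so. A pre–post change needs repeated MAP measurements, so MAP has its own follow-up selection, and its handling may sit in the full plan. What stands is narrower: MAP has no counterpart to engagement in MHC care, and no parallel completion rule is stated.

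Finally, no either-or success rule is written down. Choosing the more favourable result is something the wording allows; it is not a stated plan.

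**Conclusion.** The point holds in a limited form. Two cohorts share primary status without ranking. One is selected on post-baseline engagement and completion, with no engagement counterpart in MAP and no stated completion rule for MAP. The two IPCW statements differ in scope and must be reconciled.

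Under the assumptions in the working, baseline-only IPCW leaves about 0.1 to 0.7 PHQ-9 points, material at the upper end beside detectable effects of 0.94 to 1.43. A correct weight model brings it near 0. The error from treating either result as primary is at most about 8%, and less once the shared control and centres are counted. The missing ranking is the firmest part of the finding; the sizes are illustrations. The plan should be changed, and doing so needs no new data.

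**What to change.** - Name the all-enrolled (care initiators) cohort as the single primary analysis.
- State in the Patients section that IPCW applies to that cohort, in line with the missing-data section.
- Make the retained-in-care cohort a supportive analysis, and apply the same survey-completion rule to MAP within it.

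The cost is wording, one more weight model, and one fewer headline result.

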##### Sample size calculation

We will recruit a prospective longitudinal cohort via a non-probability sampling technique. Each participating MHC representing a cluster because patient outcomes are expected to be correlated within centers due to shared staff, resources and local community. Approximately 400 patients for the 8 MHCs (targeting ~50 per MHC) will be enrolled in the quantitative assessment. The primary outcome is the change in depressive symptoms measured by the Patient Health Questionnaire-9 (PHQ-9) scale from baseline to follow up 4 (approximately one year) (22).

We estimated the variance of the PHQ-9 change score empirically as:

$$\mathrm{Var}\;(\Delta )=\sigma_{b}^{2}+\sigma_{f}^{2}-2r\sigma_{b}\sigma_{f}\;$$

Where 
$\sigma_{b}=5.97$
 and 
$\sigma_{f}=5.50$
 are the baseline and follow-up 4 standard deviations (SDs), respectively, and 
r=0.546
 is the within-person correlation. Substituting these values gives 
Var(Δ)≈30.0
, yielding 
${\mathrm{SD}}_{\Delta }\approx 5.48$
.

We account for clustering between MHCs using design effect,

DE=1+(m−1)ICC

Where m = 50 is the average cluster size and ICC is the intraclass correlation. Under this framework (two-sided significance level 5 and 80% power), the minimum detectable difference in difference (DiD) effect in PHQ-9 points is approximately 0.94, 1.08, and 1.43 for ICC = 0.01, 0.02, and 0.05, respectively.

We will invite a subsample from the quantitative cohort of patients to interviews through a purposive sampling strategy (23). Patients will be selected with varying treatment exposure (≥1 session) to capture diverse treatment experiences and outcomes. The qualitative sample size will be guided by content saturation.

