##### Patient

Eligible patients for the cohort will receive a flyer during their regular visit at the MHC, containing essential study information with a QR code directing them to a Research Electronic Data Capture (REDCap) registration form (26, 27). We will assess the eligibility based on the submitted registration data. Eligible participants will then be contacted via their preferred way of communication and provided with a personalized link to provide informed consent and complete the self-administered quantitative assessment instruments. Follow-up assessments will be conducted via REDCap at three- and six-month intervals after baseline.

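### No coefficient named in the patient DiD analysis is tied to the declared primary outcome, PHQ-9 change to follow-up 4

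*Protocol article*

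**What the plan says.** Three places in the protocol article bear on this.

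- **Sample size calculation.** "The primary outcome is the change in depressive symptoms measured by the Patient Health Questionnaire-9 (PHQ-9) scale from baseline to follow up 4", which the article places at about one year. The variance, design effect and minimum detectable DiD all rest on that single change.
- **Quantitative data collection, Patient.** "Follow-up assessments will be conducted via REDCap at three- and six-month intervals after baseline". No one-year patient visit is scheduled here.
- **Data analysis, Patients.** The effect is obtained by "comparing pre–post changes in outcomes between MHCs and the MAP cohort, depending on outcome availability and harmonization", "with the DiD estimand given by the treatment-by-post (or treatment-by-time) interaction". The next sentence reads: "Where multiple follow-ups are available, we will implement an event-study specification (baseline, follow-up 1, follow-up 2". Follow-up 4 is not among the visits listed.

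The Maintenance dimension (RE-AIM operationalization, Table 5) lists PHQ-9 among long-term outcomes for a future phase at least six months after the second phase. The article does not say that this phase supplies follow-up 4, and it gives no model for it.

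**The concern.** A primary outcome is delivered by a specific model term. Here the outcome is a change to one late visit, while the model is described by two interaction forms and a visit list that stops before that visit.

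With one post-baseline wave, the two forms are the same. With several, a treatment-by-time interaction gives one effect per visit, and a single post indicator gives an average over visits. The article expects at least two follow-ups, so the difference is live.

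The findings are meant to guide national scale-up. An effect averaged over follow-up, an effect at six months and an effect at one year can support different conclusions if benefit accumulates or wears off. The article says that analytic results are shared with stakeholders at each phase, so the primary contrast should be tied to its time point before those results are seen.

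**Working it through.** **1. The plan's own figure.** Inputs from the sample size section: SDs 5.97 (baseline) and 5.50 (follow-up 4), correlation 0.546, 400 patients, clusters of 50, two-sided 5%, 80% power.

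- Var(change) = 5.97² + 5.50² − 2 × 0.546 × 5.97 × 5.50 = 30.04; SD = 5.48.
- Design effect = 1 + 49 × ICC = 1.49, 1.98, 3.45 for ICC 0.01, 0.02, 0.05.
- Minimum detectable effect = (1.96 + 0.84) × 5.48 × √(DE/400) = 0.94, 1.08, 1.43.

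These match the article. They belong to the single baseline-to-follow-up-4 change and to no other contrast. (They carry no variance term for the MAP control, which is a separate matter.)

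**2. Sections side by side.**

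| Section | Patient time points |
|---|---|
| Sample size calculation | baseline, follow-up 4 (about one year) |
| Data collection, Patient | baseline, 3 months, 6 months |
| Data analysis, Patients | baseline, follow-up 1, follow-up 2 |

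The time point that defines the primary outcome appears only in the first row.

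**3. Pooled term, two visits.** Assumptions: equal standard errors, correlation r between the two visit-specific DiD contrasts, the final-visit contrast powered at 80% (noncentrality 2.80), and a normal critical value of 1.96. Let f be the follow-up 1 effect as a fraction of the final effect. The pooled noncentrality is 2.80 × [(1 + f)/2] / √[(1 + r)/2].

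- f = 0.5, r = 0.5: 2.80 × 0.75 / 0.866 = 2.42; power = Φ(2.42 − 1.96) ≈ 68%. For r = 0.3 it is about 74%, and for r = 0.7 about 63%.
- f = 1, r = 0.5: 2.80 / 0.866 = 3.23; power ≈ 90%.
- Effect of 2.8 SE at follow-up 1 and none at the final visit, r = 0.5: 1.40 / 0.866 = 1.62; the pooled term is significant about 37% of the time (41% for r = 0.3, 33% for r = 0.7).

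**4. Same question on the plan's own scale.** Assumptions: visits at 3, 6, 9 and 12 months; a true effect of 1.08 points at follow-up 4 that builds linearly; ICC 0.02; every follow-up with SD 5.50 and correlation 0.546 with baseline; correlation between follow-ups from 0.546 to 0.9. For an average of n visits, Var = 5.97² + 5.50² × [1 + (n − 1) × ρ]/n − 2 × 0.546 × 5.97 × 5.50, with ρ the correlation between follow-ups.

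| Contrast | True value | SD of change | Power |
|---|---|---|---|
| Follow-up 4 | 1.08 | 5.48 | 80% |
| Average of follow-ups 1–4 | 1.08 × 0.625 = 0.68 | 4.44–5.27 | 58–44% |
| Average of follow-ups 1–2 | 1.08 × 0.375 = 0.41 | 4.81–5.34 | 22–19% |
| Follow-up 2 alone | 1.08 × 0.5 = 0.54 | 5.48 | Φ(1.40 − 1.96) ≈ 29% |

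The last row matters because follow-up 2 is the latest coefficient in the event study as listed. If the effect is constant, every contrast has the same true value, 1.08.

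**The case against.** The strongest reply is that the two interaction forms are conditional, not a free choice. The paragraph covers every patient outcome, subject to what MAP offers. Treatment-by-post suits one post wave and treatment-by-time suits several, and the event-study sentence that follows says as much. Fitted to baseline and follow-up 4 alone, treatment-by-post estimates exactly the declared outcome. The primary time point is also declared, and mapping it to a model term is often left to the analysis plan.

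Much of this stands. The article nowhere says that the post indicator pools waves, so averaging is an inference. A reader might infer that treatment-by-post can never estimate the declared outcome; the text does not support that. A reader might also infer an inflated false-positive rate from picking among several versions. The article states no joint test and no rule that any significant version counts as success, so no such rate can be attributed to it.

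What the reply does not reach is the visit list. On the conditional reading the event study governs, and it ends at follow-up 2. It yields coefficients at follow-ups 1 and 2, neither named as primary and neither the change to follow-up 4. This is a mismatch in what the article does state, and so more than detail left to another document.

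One limit remains. The article runs these analyses on two primary cohorts, so naming a coefficient does not by itself produce a single primary result.

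**Conclusion.** The point holds in this form: the article sizes the study on PHQ-9 change to follow-up 4, and no coefficient in its stated patient analysis is tied to that change. The mismatch is a matter of text and needs no assumption.

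The numerical consequences do need assumptions. They depend on how the effect evolves, on the correlation between visits, on equal standard errors and, for the pooled term, on its being fitted to all waves. With two visits and r = 0.5, power falls from 80% to about 68% when the first-visit effect is half the final one. With linear build-up over four assumed visits it falls further, to 44–58% for the average of four and 19–22% for the average of two. With a constant effect there is no bias, and pooling gains power. All these figures use normal critical values, not the planned wild cluster bootstrap over centers, and should be read as illustrations.

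**What to change.** First, reconcile the primary time point across the sample size, patient data collection and patient analysis sections, and include that visit in the event-study specification. The order matters: naming the final visit of the event study as it now stands would select follow-up 2 and conflict with the one-year primary outcome.

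Then add to the patient analysis section: *The primary PHQ-9 contrast is the treatment × primary-time-point coefficient (the visit named in the primary outcome) from the event-study model, two-sided 5%; coefficients at other follow-ups and any pooled treatment-by-post estimate are secondary.*

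If follow-up 4 is kept, the stated detectable effects of 0.94, 1.08 and 1.43 still refer to the right contrast. If another visit is chosen, the SD and correlation inputs need to be those of that visit.

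The cost is one sentence plus the reconciliation. The statistical price is lower power if the effect is constant over time: about 80% for the single-visit contrast against about 90% for the pooled term, with two visits and r = 0.5. The pooled estimate is still reported as secondary.

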### Study setting and participants

#### MHCs

We will conduct the study across the current eight MHCs and their respective communities, including four in Lviv, two in Chernivtsi, one in Dnipropetrovsk, and one in Rivne. These oblasts may differ in the mental health impact of the war, providing important contextual variation for the evaluation. Mostly, MHCs are structural components of policlinics, i.e., outpatient services. However, in Dnipro, MHC is a part of the Primary Health Care (PHC) service. While in Rivne, MHC is a hospital department within a cluster hospital, providing a network of medical services to more than one community.

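### The 1,000 bootstrap draws behind the patient-level p-values and confidence intervals leave avoidable simulation error; raising the number is a minor improvement at almost no cost

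*Protocol article*

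**What the plan says.** The Patients paragraph under Quantitative data analysis describes a difference-in-differences (DiD) comparison of MHC patients with the MAP cohort, run in two primary cohorts. On inference it says "We will obtain 95% confidence intervals" and p-values, obtained "via center-level wild cluster bootstrap (1,000 draws" being the stated number). A result with a Kenward–Roger/Satterthwaite-style degrees-of-freedom adjustment is reported as well, as a robustness check.

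On clusters, the Study setting section says "We will conduct the study across the current eight MHCs", and the Sample size calculation has "Each participating MHC representing a cluster", with about 50 patients in each. The same section uses a 5% two-sided level and 80% power.

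The article names no weight distribution, seed or enumeration rule for the bootstrap, and does not say how MAP participants form clusters. A condensed article may leave these to a fuller document, so their absence is not part of this point. The number of draws is different, because the article prints it.

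**The concern.** A bootstrap p-value is the share of draws whose test statistic is at least as extreme as the observed one. With 1,000 draws, about 50 determine whether p falls on one side of 0.05 or the other. Repeating the analysis on the same data with another seed changes that count, and so the p-value and the interval limits. The p-value and interval meant to inform refinement and scale-up of the centers would then carry noise that comes from neither patients nor centers and that computing time alone can remove.

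**Working it through.** **Inputs from the article.** B = 1,000 draws; 8 MHCs of about 50 patients; two-sided 5% level and 80% power; baseline and follow-up SDs 5.97 and 5.50, correlation 0.546; ICC 0.01, 0.02 or 0.05.

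**The article's own figures.** It states no Monte Carlo precision, so there is none to reproduce. Its outcome variance does reproduce: 5.97² + 5.50² − 2 × 0.546 × 5.97 × 5.50 = 30.04, SD 5.48. So do its minimum detectable effects: 2.80 × 5.48 × √((1 + 49 × ICC)/400) = 0.94, 1.08 and 1.43 points. The SD and the ICC of 0.02 feed the simulation below.

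**Monte Carlo error of p.** SE = √(p(1 − p)/B). The number of clusters does not enter.

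| Draws | SE at p = 0.05 | 95% range over seeds |
|---|---|---|
| 1,000 | √(0.05 × 0.95/1,000) = 0.0069 | 0.036 to 0.064 |
| 9,999 | 0.0022 | 0.046 to 0.054 |
| 99,999 | 0.0007 | 0.049 to 0.051 |

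**Chance that the seed moves p across 0.05.** The count of extreme draws is binomial(B, p); a reported p at or below 0.05 counts as significant.

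- Bootstrap p = 0.045: reported above 0.05 with probability 0.199 at 1,000 draws and 0.009 at 9,999.
- Bootstrap p = 0.055: reported at or below 0.05 with probability 0.270 at 1,000 draws and 0.013 at 9,999.
- At p = 0.03 or 0.07 the verdict holds in more than 99% of seeds, even with 1,000 draws.

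**How often this matters.** Averaging the binomial tails over a normally distributed test statistic (an approximation), at 1,000 draws:

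| Situation | p falls in 0.037–0.064 | Verdict differs from infinite draws | Two seeds disagree |
|---|---|---|---|
| No effect | 2.7% | 0.6% | 0.8% |
| 80% power | 6.6% | 1.3% | 1.8% |
| 50% power | 9.3% | 1.9% | 2.6% |

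**Interval width.** A restricted wild cluster bootstrap was run on one simulated data set per layout (8 centers of 50, SD 5.48, ICC 0.02, effect set so that p was near 0.05). The MAP structure was assumed: its mean taken as fixed, or MAP entered as 1, 4 or 24 clusters. Two-point and six-point weights were both tried.

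- At 1,000 draws the seed SD of p was about 0.007 to 0.008 in every layout, in line with the formula.
- The seed SD of the interval width was about 2.5% to 6% of the width at 1,000 draws and 0% to 1.5% at 9,999.
- The widest spread came with 8 clusters and two-point weights: 1.35 to 1.69 points over 60 seeds, against 1.57 by full enumeration.

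**Enumeration.** Two-point weights over 8 clusters give 2⁸ = 256 sign patterns, fewer than the planned 1,000 draws. Patterns that differ only in overall sign share the same absolute t, which leaves 128 distinct values. The p-value then moves in steps of 1/128 = 0.0078; around 5% the attainable values are 6/128 = 0.0469 and 7/128 = 0.0547.

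**The case against.** The strongest reply is that this is close to a tuning preference. A borderline p must occur before the seed matters, which is uncommon. The point estimate never changes. A width that varies by a few percent is small beside the article's own uncertainty about the ICC, which moves the minimum detectable effect from 0.94 to 1.43 points. The degrees-of-freedom-adjusted result uses no random draws, so a reader facing a borderline bootstrap p has a seed-free result beside it. The article also states no decision rule at 5% beyond the power calculation. All of this stands, and it is why the point is minor.

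Three stronger readings are tempting but not supported. A reader might infer that having only eight centers causes the seed dependence. It does not: Monte Carlo error is set by the number of draws, and the eight centers matter here only because they make enumeration possible. A reader might infer that the main conclusion is unreliable; the table of rates shows otherwise. A reader might also take enumeration as plainly better than sampling. It removes the seed, but its step of 0.0078 is larger than the standard error of 0.0069 that it removes, and it applies only to two-point weights, which the article does not specify.

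What the reply does not remove is that the printed figure of 1,000 can be raised at almost no cost.

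**Conclusion.** The point holds as a minor improvement. With 1,000 random draws the p-value has a Monte Carlo SE of 0.0069 at 0.05, and a p between about 0.037 and 0.064 may be reported on either side of 5% depending on the seed. Over all studies the verdict changes in roughly 0.6% under no effect and 1.3% at 80% power.

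The SE and the flip rates need only the plain reading that the draws are random. The overall rates rest on a normal approximation. The interval-width figures rest on a simplified simulation with an assumed MAP structure and without the planned inverse probability weighting, so they indicate order of size only.

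**What to change.** In the Patients paragraph, replace the figure of 1,000 with at least 9,999 draws, preferably 99,999, and a seed set in advance. The seed makes the result reproducible; only the larger number of draws reduces the error.

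If the analysis uses two-point weights over only eight clusters, all 256 sign patterns may be enumerated instead, provided the plan acknowledges that p then moves in steps of 0.0078. Six-point weights with many draws avoid that coarseness.

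The cost is one line of text and minutes of computing. Data, estimand and point estimate are unchanged.
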